### Randomization and allocation concealment procedure

Computer-generated random allocation sequence (1:1 ratio) will be created using statistical software (SAS) by an independent individual who is not involved in participant recruitment, thereby ensuring that investigators cannot access or influence the original sequence. Allocation concealment will be implemented using opaque, sealed kraft paper envelopes that prevent visualization of contents under light. Each envelope will be labeled with a unique participant number corresponding to the randomization sequence but will not contain any indication of group assignment on the exterior. The printed group assignment will be folded, placed inside the appropriately numbered envelope, and sealed. An additional transparent outer sleeve (marked as “Unopened”) will be applied over the envelope, ensuring integrity through double sealing. Once a participant meets all eligibility criteria and signs the informed consent form, the researcher will provide the participant’s basic information to the coordinator and request the corresponding sequentially numbered envelope. After verifying the information, the coordinator will take out the corresponding envelope in numerical order. The envelope will be opened on-site by the researcher, and the intervention will be implemented according to the grouping information inside. After opening, the date, time, and signature of the person who opened the envelope must be marked on the envelope, which will then be archived for documentation.

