### Patient recruitment

Patient recruitment follows a four-step procedure;

Step 1: Promotion for inpatient recruitment will be conducted through outpatient clinics, among inpatients, and at surrounding community service centers.

Step 2: A clinical research assistant will assess potential participants for eligibility according to the predefined inclusion and exclusion criteria.

Step 3: The study coordinator will schedule an interview with eligible individuals to provide detailed information about the study objectives, procedures, potential risks and benefits.

Step 4: Participants who fully understand the study information and voluntarily agree to participate will provide written informed consent. The written informed consent form is provided in **Supplementary Material S2**.

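### The envelope is marked only after opening and with no patient entry, so the record does not show that the patient was bound to it before the allocation was known

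*Protocol article*

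**What the plan says.** All references are to the protocol article.

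**Randomization and allocation concealment procedure.** The sequence is created "by an independent individual who is not involved in participant recruitment". The envelopes are opaque, sealed, labelled outside with a participant number tied to the sequence, and covered by a transparent outer sleeve marked as unopened. The order of events is then:

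1. "Once a participant meets all eligibility criteria and signs the informed consent form, the researcher will provide the participant’s basic information to the coordinator", and asks for the envelope.
2. "After verifying the information, the coordinator will take out the corresponding envelope in numerical order".
3. "The envelope will be opened on-site by the researcher", and the intervention follows the assignment inside.
4. "After opening, the date, time, and signature of the person who opened the envelope must be marked on the envelope". The envelope is then archived.

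**Patient recruitment, Step 3.** "The study coordinator will schedule an interview with eligible individuals to provide detailed information about the study objectives", along with procedures, risks and benefits.

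**Blinding.** Participants are blinded. The investigators who give the stimulation and those who rate outcomes are not.

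**Table 1.** Randomization is ticked at Day -1. Allocation and the baseline HAMD-17, BDI-II and C-SSRS are ticked at Day 0.

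**The concern.** Sealed envelopes protect against selection bias only if the patient is irrevocably committed before the content is known. The usual proof is an entry made on the envelope while the seal is intact. Here the one required entry comes afterwards and names the opener, not the patient. The stated separation from recruitment also ends once the list has been generated.

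The stakes are higher than in a double-blind trial. Once the envelope is open, the treating and rating staff know the arm, so concealment up to assignment is the main protection the design has against selection bias. The primary outcome, a HAMD-17 reduction of at least 50%, is measured from a baseline score, so it also matters that this score is fixed before the arm is known.

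**Working it through.** The document gives no figure to reproduce on this point. The check sets its statements side by side.

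**Who is independent of recruitment?** The randomization section says so only of the list generator. The dispenser is called the coordinator, and the recruitment section has a study coordinator arrange the information interview. Taking these as the same role is the natural reading, but it is an assumption. Under Data management, the study coordinator also looks after the stored paper CRFs and study documents.

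**What ties a patient to an envelope before opening?** There are three candidates:
- *The pre-printed participant number.* It ties the envelope to a position in the sequence, not to a person. Data management assigns each participant an identification number upon enrollment, without saying whether that comes before opening.
- *The details given to the coordinator.* This is a real step before opening: a second person learns who the patient is and verifies the details. The text does not say that this is written down or later compared with the envelope.
- *The marking on the envelope.* It comes after opening and consists of date, time and the opener's signature.

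Only the second candidate binds the patient in advance, and it leaves no stated record.

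**Which routes to a steered assignment stay open?**
- *Looking inside early.* Opaque paper, the seal and the outer sleeve stand in the way, and a premature opening would show.
- *Taking envelopes out of order.* The numbering and the rule to use them in order stand in the way.
- *Opening in proper order and then deferring, excluding or replacing the patient.* The seal is properly broken and the numbers run on. The envelope entry would look the same as for an undisturbed assignment. The only obstacle is what the coordinator knows.

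The third route is the one that an entry across the intact seal would close.

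**Are baseline scores fixed before release?** The stated trigger for requesting an envelope is eligibility plus signed consent. Table 1 has randomization on Day -1 and the three scales on Day 0, while the Figure 1 legend equates T0 with both baseline and randomization. Eligibility requires a HAMD-17 of at least 17 and a C-SSRS ideation score of at least 3, so some scores must exist beforehand. But the schedule shows no scale at enrollment, and the text does not say that the eligibility score is the baseline used for response. As written, the baseline is not clearly recorded before the envelope is opened.

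**The case against.** The strongest reply is that this is a conventional and fairly careful envelope procedure. The patient is identified to a second person, who verifies the details before the envelope is taken out. One person generates the list, another dispenses the envelope and a third opens it. The coordinator's recruitment task is only to schedule an interview: a research assistant checks eligibility, two physicians do the screening and assessment, and handling a sealed opaque envelope reveals nothing. An article may also leave storage and logs to the full protocol.

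Most of this stands and sets the limit of the point. The reply does not change the marking rule, which the article states explicitly and which comes after opening with no patient entry.

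Three stronger readings are tempting and are not supported:
- *That an allocation can be seen in advance, or a patient swapped without trace.* Early opening would break two layers. A later swap would conflict with what the coordinator was told, and would need that person's cooperation or silence.
- *That the coordinator holds the envelope stock, or that the opener also delivers the stimulation.* The text says only that the coordinator takes the envelope out, and it names no one as delivering the intervention. Both are inferences.
- *That the trial's size shows the harm.* With 28 per arm, moving one certain responder into active and one certain non-responder into sham shifts the difference in response rates by 1/28 + 1/28 = 7.1 percentage points. That is a hypothetical ceiling for any trial with 28 per arm. It is no evidence that this procedure fails.

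**Conclusion.** The point holds as a moderate procedural weakness. The written record does not show that the patient was bound to the envelope before the allocation was known, and the envelopes pass through a role with a recruitment task. Unblinded treating and assessing staff make a clean record more valuable here, although unblinding after assignment does not itself show that concealment fails.

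No breach of concealment is shown, and no effect on the response-rate comparison can be derived from the document. The part about custody assumes that the coordinator in the two sections is the same role. The part about timing assumes that Table 1 is meant literally. The part about the marking rule needs neither assumption. The change should be made because the gap is real and closing it costs very little.

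**What to change.** Amend the randomization section as follows:

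1. Before opening, write participant number, date, time and signature across the intact seal. Add the opening time afterwards.
2. Release the envelope only after eligibility and the baseline HAMD-17, BDI-II and C-SSRS scores have been recorded. Bring the Day -1 and Day 0 entries of Table 1 and the Figure 1 legend into line with that order.
3. Where feasible, have the independent list generator release the envelopes in place of the coordinator.

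The cost is a few sentences of procedure and a small correction to the schedule. The independent person already exists; the one practical downside is that this person must be reachable whenever a patient is randomized. If that is not workable, items 1 and 2 can stand alone and close most of the gap. If the full protocol already requires them, only the marking sentence and the schedule in the article need correcting.

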### Blinding

This study employs a single−blind design, in which participants will remain blinded to their treatment allocation (active or sham stimulation), while investigators administering the interventions and assessing outcomes will not be blinded due to the technical requirements of transcranial magnetic stimulation (TMS). Blinding of participants is critical to minimize expectancy effects and subjective reporting biases. Unblinding will be permitted only in cases of serious adverse events where knowledge of treatment allocation is required for clinical management. In all other circumstances, the blinding will be maintained until database lock and completion of the primary analysis.

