## Materials and methods

### Study design

This randomized, sham-controlled clinical trial was approved by the Ethics Committee of Wuxi Mental Health Center and prospectively registered in the Chinese Clinical Trial Registry (ChiCTR; official website: www.chictr.org.cn, Registration No.: ChiCTR2500109181). All procedures will adhere to the principles of the Declaration of Helsinki and the Guidelines for Good Clinical Practice (GCP). Reporting will follow the SPIRIT 2025 recommendations, and the completed SPIRIT checklist is available in **Supplementary Material S1**.

This trial will be conducted at Wuxi Mental Health Center between September 2025 and August 2027. The assessment and screening will be conducted by two practicing physicians from Wuxi Mental Health Center. Eligible participants will be randomly allocated (1:1) to receive either active sequential accelerated theta burst stimulation (aTBS; 3,600 pulses per session, 10 sessions total) or sham stimulation. Outcome measures will include the 17-item Hamilton Depression Rating Scale (HAMD-17) (24), Beck Depression Inventory (BDI-II) (25), Columbia Suicide Severity Rating Scale (C-SSRS) (26), Treatment Emergent Symptom Scale (TESS) (27) and event-related potential P300. All assessments will be administered at baseline (T0), immediately after the final stimulation session (T1), and at 2-week (T2) and 4-week (T3) follow-ups. A detailed flow diagram of the trial is shown in **Figure 1**, and the trial schedule is presented in **Table 1**.

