**Figure 1 f1:**
[figure not shown]
CONSORT flow diagram of the study protocol; Patient screening; Depressed patients (n=56); Randomized allocation; Active stimulation group (n=28); Sham stimulation group (n=28); T0, baseline (randomization); T1, post-intervention; T2, 2-week follow-up; T3, 4-week follow-up; HAMD-17, 17-item Hamilton Depression Rating Scale; BDI-II, Beck Depression Inventory-II; C-SSRS, Columbia-Suicide Severity Rating Scale; aTBS, accelerated theta-burst stimulation.

**Table 1 T1:** Detailed trial schedule.

	Study period							
	Enrollment	Allocation	Post-allocation				Follow-up 1	Follow-up2
Time point	Day-1	Day 0	AFT	Day1	~	Day 10 (Intervention period)	Week2	Week4
Enrollment:								
Eligibility screen	×							
Informed consent	×							
Randomization	×							
Allocation		×						
Interventions:								
Conventional treatment + sequential aTBS								
Conventional treatment + sham sequential aTBS								
Assessments:								
HAMD-17		×				×	×	×
BDI-II		×				×	×	×
C-SSRS		×				×	×	×
P300		×				×		
Case report forms	×							
Adverse events								
TESS								
Blinding			×					
TASS	×							
ATHF	×							

AFT; Immediately post-allocation (after randomization and before the first intervention); HAMD-17, 17-item Hamilton Depression Rating Scale; BDI-II, Beck Depression Inventory-II; C-SSRS, Columbia-Suicide Severity Rating Scale; P300, Electroencephalography; ATHF, Antidepressant Treatment History Form; TASS, Transcranial Magnetic Stimulation Safety Screen; TESS, Treatment Emergent Symptom Scale ×, occurs at that time.

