Participants in the active group receive sequential bilateral aTBS twice daily for 10 treatment days. The interval between the two daily treatment sessions in this study is set at 3 hours This interval is based on the following considerations: (1) Safety: Drawing on experience from the SAINT protocol, a 3-hour interval provides sufficient safety redundancy (12); (2) Neurophysiological recovery: This interval allows the nervous system to recover from each stimulation session, avoiding excessive cumulative effects (30); (3) Tolerability: It reduces fatigue and discomfort, thereby improving treatment adherence. The aTBS protocol, illustrated in **Figure 2**, consists of cTBS applied to the right DLPFC followed immediately by iTBS applied to the left DLPFC. Specifically, cTBS delivers 1,800 pulses over 120 seconds, whereas iTBS consists of three trains of 600 pulses (3 minutes and 9 seconds each) separated by 10-second intervals, totaling 1,800 pulses over 570 seconds. The coil is positioned tangentially to the scalp with the handle pointing posterior–laterally at approximately 45°. Sham stimulation will be delivered by tilting the coil 90° away from the scalp, while maintaining identical stimulation targets, treatment duration, and procedural protocols to those of the active intervention. This sham stimulation protocol is widely accepted and utilized in clinical trials (31).

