### Study outcomes

#### Primary outcome

The primary outcome is to compare the response rate of depressive symptoms between the active stimulation group and the sham stimulation group after intervention. The response rate is defined as a reduction of 50% or more in the HAMD-17 score compared with the baseline. Remission is defined as a HAMD-17 score of ≤ 7 (32).

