Several limitations of this study must be acknowledged. This is a single-center investigation with a modest sample size. The single-blind design employed in this study may introduce potential investigator bias. Regarding the limitations of the sham stimulation method, this study employs the coil tilting method as the sham control condition. Although this method is widely used, it has limitations, including incomplete matching of somatosensory experience and lack of operator blinding, which may potentially impact participant blinding. To assess the extent of blinding compromise, we will conduct a blinding integrity check after the intervention and incorporate sensitivity analyses into the statistical analysis to examine the robustness of the results. Future studies should adopt dedicated sham coils and double-blind designs to further reduce the risk of bias. The mechanistic analysis based on EEG is exploratory in nature and cannot establish causal inference. Nonetheless, these design choices reflect a balance between feasibility and scientific rigor, providing essential preliminary data to inform future multicenter trials. In conclusion, this study is expected to yield valuable clinical and safety evidence for sequential aTBS as a rapid and well-tolerated intervention for suicidal ideation in adults with MDD.

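### Outcome raters are left unblinded for a reason that applies to the coil operator, so rater expectation can bias the HAMD-17 primary outcome

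*Protocol article*

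**What the plan says.** The Blinding section describes a single-blind design. Participants are masked, "while investigators administering the interventions and assessing outcomes will not be blinded due to the technical requirements of transcranial magnetic stimulation (TMS"). One reason therefore covers two roles, stimulating and rating. The aTBS protocol section describes the sham: "Sham stimulation will be delivered by tilting the coil 90° away from the scalp". Study design says who rates: "The assessment and screening will be conducted by two practicing physicians from Wuxi Mental Health Center".

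On the primary outcome: "The response rate is defined as a reduction of 50% or more in the HAMD-17 score compared with the baseline". The Abstract also lists remission, which is a HAMD-17 threshold. C-SSRS and TESS are described as administered or rated by a clinician. BDI-II is self-reported.

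On timing, Table 1 marks randomization on Day -1 and the first HAMD-17 and C-SSRS on Day 0, under Allocation. The Figure 1 legend has "T0, baseline (randomization"). The randomization section has the researcher open the envelope once eligibility and consent are complete.

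The Discussion concedes: "The single-blind design employed in this study may introduce potential investigator bias".

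**The concern.** The stated reason does not support the stated decision. A tilted coil cannot be hidden from the person holding it, but HAMD-17 and C-SSRS can be scored by someone who never sees it. The section itself treats expectancy and subjective reporting as reasons to mask participants. The same reasoning applies to the person who scores the primary endpoint.

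Response is a threshold on a rated score, so a small, unintended leniency towards one arm turns near-misses into responders. No later analysis can remove that from the recorded scores. A positive primary result would then be open to the explanation that the raters knew the arm.

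**Working it through.** **Step 1: does the reason reach the raters?**
- The only technical obstacle described is the coil tilt (aTBS protocol).
- Scoring at T1, T2 and T3 involves no coil.
- Two physicians assess and screen (Study design). No section says that they stimulate.
- The envelope is opened by an unspecified researcher (randomization section). Nothing keeps the raters away from that step.

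The raters' lack of masking is therefore a choice, not a technical necessity.

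**Step 2: how far could leniency move the primary outcome?** The plan has no figure of its own to reproduce. From the document: 50 participants required, so 25 per arm, and the 50% rule. Assumed: baseline H0 normal with mean 24 and SD 4, values below 17 set to 17 (17 is the entry threshold); fall normal with mean 8 and SD 6; no true effect.

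A patient counts as a responder if (H1 − s) ≤ 0.5 × (H0 + b). Here s is the points scored too low at T1 and b the points scored too high at baseline, both in the active arm only.

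Hand check at H0 = 24: response needs a fall of at least 12 − s.
- s = 0: 1 − Φ((12 − 8)/6) = 1 − Φ(0.667) = 25%
- s = 2: 1 − Φ((10 − 8)/6) = 1 − Φ(0.333) = 37%

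Over the whole baseline distribution, rates were obtained by simulation. The rejection rate was then summed exactly over all pairs (a, c) of responder counts, with weights Bin(a; 25, p_active) × Bin(c; 25, p_sham). The chi-square test rejects when |a − c|/25 ÷ √(2p̄(1 − p̄)/25) > 1.96, where p̄ = (a + c)/50.

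| s (points) | Response, active vs sham | Chi-square | Fisher's exact |
|---|---|---|---|
| 0 | 26% vs 26% | 5.4% | 2% |
| 1 | 32% vs 26% | 7.5% | 3% |
| 2 | 37% vs 26% | 14.4% | 8% |
| 3 | 44% vs 26% | 26.8% | 17% |

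Both tests are shown because the clinical analysis section allows either.

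**Step 3: other assumptions.** With baseline mean 23, SD 4, floor 17, and a mean proportional fall of 25% to 45% (SD 28%), true response runs from 20% to 44%. A 2-point leniency then gives 14% to 17% by chi-square and 7% to 11% by Fisher's test.

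**Step 4: the baseline end.** In the responder rule b is halved, so a baseline point counts half as much as a T1 point. Under the Step 2 inputs, b = 1 alone gives 5.9% and b = 2 alone gives 7.5% (chi-square).

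**Step 5: is the baseline rated after the arm is known?** Table 1 puts randomization a day before the first marked HAMD-17. Against that, HAMD-17 ≥17 and C-SSRS ≥3 are entry criteria, the eligibility screen is marked on Day -1, and the envelope follows eligibility. Some score must therefore precede it. The separate post-allocation column (AFT) has no HAMD-17 mark, and the order of rating and envelope opening on Day 0 is not given. The sections do not settle which score is the baseline or whether it precedes opening.

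**The case against.** The strongest reply is that the trade-off is declared. The trial is called exploratory, the Discussion admits possible investigator bias, and it plans a blinding check and sensitivity analyses. BDI-II, scored by masked participants, is already collected at all four time points. This stands in part: the limitation is not hidden, and BDI-II offers a useful comparison. But the check and the sensitivity analyses are introduced for the sham's effect on participant blinding. Neither they nor BDI-II can correct a biased HAMD-17 rating.

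A second reply is that the error rates rest on assumed inputs and assumed leniency. That stands. At 1 point the inflation is small, and Fisher's test, which is conservative here, stays below 5%.

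A reader might also infer from Table 1 that baseline is rated with the arm known, so that both ends of the primary outcome are biased. The documents do not support that. The Day 0 order is unstated and an earlier screening score is implied. Table 1 as extracted also has rows with no marks at all, so its columns should be read with caution. What remains is a possibility, with the smaller effect shown in Step 4.

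Nor do the documents show that masking needs no extra staff, since team size is not given, or that this is the worst avoidable bias in the trial.

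**Conclusion.** The point holds for the raters. The plan leaves assessors of the primary outcome, C-SSRS and TESS unblinded on a ground that applies to the operator, and nothing planned corrects the resulting bias. Under the Step 2 assumptions, leniency of 2 to 3 points after treatment raises the false-positive rate from 5% to about 14% to 27% by chi-square, or from 2% to about 8% to 17% by Fisher's test. These figures show sensitivity. They do not predict that raters will be lenient. The baseline timing is a matter to reconcile, not an established bias. The rater point should be fixed before ratings are made, because it cannot be repaired afterwards.

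**What to change.** 1. In Blinding, confine the technical reason to operators and state that the two assessing physicians stay blind to allocation. They do not open envelopes, stimulate, enter the treatment room or see treatment logs, and participants are asked not to discuss sensations with them. Other members of the existing team open envelopes and stimulate.
2. Code the EEG files so that component rejection and P300 peak picking are done blind to arm. The existing participant IDs protect identity, but the article does not say that they mask the EEG analyst.
3. Reconcile Table 1 and the Figure 1 legend with the eligibility criteria and the randomization section. Name the HAMD-17 score that serves as baseline, and state that baseline ratings are completed and locked before the envelope is opened.

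The cost is a rewritten paragraph, an edited table and rota planning to keep raters and operators apart. Sample size and visit schedule need not change. The sponsor should confirm that existing staff can cover the separated roles.
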